#### Inertial Data Labeling

The researchers will attend a supervised physiotherapy session for each patient once every 2 weeks to record exercise type and technique labels synchronously with inertial data collection, based on the input from the treating physiotherapist. The technique will be labeled as a binary variable, indicating if the treating physiotherapist was satisfied that the exercise was performed correctly (as intended). The treating physiotherapist will also make a record of prescribed home exercises and exercise type and technique evaluations at each supervised physiotherapy session.

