#### Barriers to Adherence

The following potentially significant adherence predictors [12,105-110] will be collected for each patient at recruitment: age, sex, body mass index, dominant side involvement, symptom duration, mechanism of injury (traumatic or degenerative), rotator cuff tear thickness and size, type of operative procedures, comorbidity (cumulative illness rating scale [111]), smoking status, alcohol intake, opioid intake, cannabinoid intake, the baseline level of physical activity, education, marital status, job demands, socioeconomic status (current income), perceived social support (Enhancing Recovery in Coronary Heart Disease Social Support Inventory [112]), patient self-efficacy (2-item Pain Self-Efficacy Questionnaire [113]), Patient Expectation Questionnaire [114], and Hospital Anxiety and Depression Scale [115].

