#### Smart Physiotherapy Activity Recognition System-Home Physiotherapy Technique Adherence

A second supervised learning algorithm will be trained, validated, and optimized to classify the exercise technique from the labeled inertial sensor data collected during the supervised physiotherapy sessions. We anticipate that a CRNN architecture similar to the exercise type classifier will likely be suitable. The validated technique classifier will be used to evaluate the technique adherence from the inertial data collected during unsupervised home sessions.

Anticipated challenges with the proposed supervised learning approach to technique evaluation include class imbalance and recovery-related changes in exercise performance. It is anticipated that many more correct technique training examples may be available for some exercises and that an exercise may be performed incorrectly in ways not observed during the supervised sessions, leading to class imbalance. It is also anticipated that through recovery, the expectation for technique and performance of an exercise may change over time, creating a moving target for the technique classifier. The challenge of class imbalance may be mitigated using several potential approaches including (1) random over and undersampling [117]; (2) cost-sensitive learning [117]; (3) semisupervised learning [118]; (4) anomaly detection [119,120]; and (5) synthetic data augmentation [121]. The challenge of recovery-related performance changes may be mitigated by providing our technique classifier metadata related to the classification task (eg, treatment week, pathology, and surgery) [116], implementing patient-specific ML models using transfer learning, and periodically retraining the ML models through recovery.

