#### Criterion Validity

Changes in clinical outcomes will be evaluated as a function of SPARS adherence measures using univariate linear regression analysis, with management subgroup (conservative or operative) and population subgroup (worker or patient) as moderators. This analysis will examine both the concurrent and predictive effects of home physiotherapy adherence on clinical outcomes.

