#### Univariable and Multivariable Analyses

The relationship between adherence (dependent variable) and individual baseline adherence predictor variables and environment (home or clinic) will be examined using parametric univariable statistical analyses, linear regression for continuous predictors, and 2-sample *t* tests and analysis of variance for binary and multiclass categorical predictors. A multivariable analysis will be conducted to model adherence from statistically significant predictors (maximum 12) and evaluate their relative importance.

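### If pathology or surgery is fed to the technique classifier, their later association with technique adherence may partly reflect the scoring; report those analyses with and without them

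*Protocol article*

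**What the plan says.** In the protocol article, the section on home technique adherence describes a classifier trained on labelled clinic sessions and then applied at home: "The validated technique classifier will be used to evaluate the technique adherence from the inertial data collected during unsupervised home sessions". The training label is the treating physiotherapist's judgement (Inertial Data Labeling): "The technique will be labeled as a binary variable, indicating if the treating physiotherapist was satisfied that the exercise was performed correctly (as intended").

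The same section expects the standard for correct technique to move as patients recover. "The challenge of recovery-related performance changes may be mitigated by" three listed means: "providing our technique classifier metadata related to the classification task (eg, treatment week, pathology, and surgery"), patient-specific models, and periodic retraining.

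Barriers to Adherence lists the candidate predictors, including mechanism of injury and "rotator cuff tear thickness and size, type of operative procedures". Univariable and Multivariable Analyses then examines "The relationship between adherence (dependent variable) and individual baseline adherence predictor variables and environment (home or clinic"). Criterion Validity regresses change in clinical outcome on the adherence measures, "with management subgroup (conservative or operative) and population subgroup (worker or patient) as moderators".

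**The concern.** A classifier that knows a patient's surgical status or pathology can learn how often clinic exercises in that group were labelled correct. It then leans towards that rate when it scores home exercises, even where the movement is the same. Surgery and pathology would help to produce the technique score, and closely matching variables would then be tested as reasons for it.

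Two conclusions are exposed. One is a claim that operative procedure, tear characteristics or injury mechanism is a barrier to good home technique. The other is the moderation by management group in Criterion Validity, where the exposure would be measured with a different error in each group.

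The planned checks do not cover this:

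- Construct Validity uses performance metrics on labelled clinic data, which such metadata can improve.
- Concurrent Validity compares technique only with physiotherapist logs. The home diaries are compared on number and type of exercises, so technique at home has no external check.
- Algorithmic Fairness looks at sex and workers' compensation status only.

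**Working it through.** **Plan's own figures.** The article gives no figure on this point. The nearest is the objective that technique classification accuracy exceed 80%. The inputs below are assumptions chosen to show the mechanism.

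**Model.** The movement score is normal with unit variance, centred at +d/2 for a correct repetition and −d/2 for an incorrect one. If movement alone has balanced accuracy a, then d = 2Φ⁻¹(a). A classifier that also knows the group's clinic rate p calls a repetition correct above t = −ln[p/(1−p)]/d. Its recall is 1 − Φ(t − d/2) and its false-correct rate is 1 − Φ(t + d/2). With true home rate h, the share called correct is h × recall + (1 − h) × false-correct rate.

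**Worked case.** Take a = 0.80, so d = 2 × 0.8416 = 1.683. True home technique is h = 0.75 in both groups. Clinic labels are 85% correct in one group and 70% in the other.

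| Clinic rate | t | Recall | False-correct rate | Called correct at home |
|---|---|---|---|---|
| 85% | −1.031 | 96.9% | 57.5% | 0.75 × 0.969 + 0.25 × 0.575 = 87.1% |
| 70% | −0.503 | 91.1% | 36.8% | 0.75 × 0.911 + 0.25 × 0.368 = 77.5% |

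The spurious gap is 87.1 − 77.5 = 9.6 points.

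**Range, with the second group's clinic rate held at 70%.**

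| Movement accuracy | 80% v 70% | 85% v 70% | 90% v 70% |
|---|---|---|---|
| 80% | 6.2 | 9.6 | 13.3 |
| 90% | 2.9 | 4.7 | 6.9 |

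Equal clinic rates give equal thresholds and a gap of zero.

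**Would clinic accuracy show it?** Compared with one pooled threshold (groups of equal size), adding the group raises overall clinic accuracy by 0.5 of a point in the worked case and by 0.1 to 0.9 points across the range. The accuracy benchmark would therefore favour the metadata model slightly and raise no alarm.

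**Effect on a test, under a second set of assumptions.** True home rate is 80% in both groups, groups are 60 v 60, the between-patient SD of technique adherence is 0.15 to 0.25, and movement accuracy is 80%, 85% or 90%.

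- Clinic rates 85% v 75%: gaps of 6.0, 4.5 and 3.0 points; a 5% test rejects 10% to 59% of the time.
- Clinic rates 90% v 70%: gaps of 12.1, 9.4 and 6.3 points; it rejects 28% to 99% of the time.
- Clinic rates 80% v 80%: no gap, and 5% rejection.

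**The same check on a classifier without metadata.** If correct movement looks the same in both groups, the gap is zero. Now let the scores sit 0.5 SD apart between groups (+0.25 and −0.25), with h = 0.75, a = 0.80 and one threshold t = −ln(3)/1.683 = −0.653. The calls are 85.1% v 75.3%, a spurious gap of 9.8 points. For separations of 0.25 to 1.0 SD and accuracy of 80% to 90%, it is 3.5 to 19.7 points.

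**The case against.** The strongest reply is that the article has not decided to use metadata. The verb is conditional, the variables are examples, two other remedies stand beside them, and the final classifier inputs could be settled in a fuller document. This stands against any reading that the plan builds these variables into the outcome. It does not remove the point: the article itself names both the possible inputs and the overlapping predictors, and a choice guided by clinic accuracy would tend to favour adding them.

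The second reply is that metadata may be right for the task. If what counts as correct differs by stage or surgery, a classifier blind to that is biased too, by as much as 9.8 points in the example above. This stands in full. A reader might infer that a metadata-free score is the unbiased reference; that holds only if correct movement looks the same in every group, and the article's remark about changing expectations for technique suggests otherwise.

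Third, the artefact is not undetectable. In the worked case recall differs by group (96.9% v 91.1%), as does the false-correct rate (57.5% v 36.8%). Equalized odds by surgical status would show it. The planned fairness analysis has the right metric but does not name that subgroup.

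Three wider inferences are tempting and unsupported:

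- Management group is not built into an outcome in Criterion Validity. The outcome there is clinical change and adherence is the exposure. The worker/patient moderator is not among the metadata examples.
- Treatment week is neither a listed predictor nor a moderator.
- Participation adherence is described with no metadata input, so it is not affected.

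**Conclusion.** The point holds conditionally, and for technique adherence only. If pathology or surgery enters the classifier, an association of technique adherence with operative procedure, tear characteristics or injury mechanism cannot be attributed to patient behaviour alone. The article contains no safeguard against this.

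The bias needs two things: clinic label rates that differ by group, and a difference that does not carry over to the home. Given both, the spurious gap is about 3 to 13 points for clinic differences of 10 to 20 points and movement accuracy of 80% to 90%. With equal clinic rates it is zero. All of these inputs are assumed, so the figures show a plausible size and are not an estimate for this study. For Criterion Validity the consequence is exposure error that differs by management group, whose effect on the moderation test is not quantified here.

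This is a cheap improvement to what the results can support. It does not show that the planned analysis is wrong as written.

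**What to change.** Add to the section on home technique adherence: if metadata such as pathology or surgery are used in the technique classifier, the technique-adherence analyses under Univariable and Multivariable Analyses, and the moderation by management group under Criterion Validity, will be reported with technique scores from classifiers both with and without the variables tested there. State also that an association with surgery or pathology seen only with the metadata model will not be interpreted as a barrier to adherence. Do not describe either model as the unbiased one.

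The cost is one extra model fit and a few sentences. The two sets of results may disagree, and the report would then have to say that the association is unresolved. The comparison does not address every route: patient-specific models, another listed option, could also absorb a patient's own clinic label rate.

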### Smart Physiotherapy Activity Recognition System–Powered Rehabilitation Program Development and Pilot Testing (Aim 3)

We will examine functional needs and ethical and related policy issues associated with the deployment of SPARS to design, implement, and pilot test novel rehabilitation strategies that provide individualized adherence-driven patient care in accordance with ethical innovation and user-centered design practices.

#### Examination of User Needs, Ethical Issues, and Policy Issues

We will complete qualitative interviews with patients, health care providers (primary care physicians, orthopedic surgeons, and physiotherapists), and policy-level stakeholders at the WCP, Workplace Safety and Insurance Board (WSIB), and the Ontario Ministry of Health and Long Term Care to examine different perspectives on individual experiences, ethical commitments, and challenges that arise, ranging from individual worker anxieties to allocation decision making regarding the distribution of limited resources to promote rehabilitation. The methodology will follow Yin’s [122] embedded single-case study methodology, wherein there is a single overarching case with 2 embedded units of analysis. The overarching case is the project, which includes the effort to generate and validate the SPARS technology, to co-design a program relying on that technology and to provide indications of acceptability and impact. The 2 embedded units of analysis will be (1) policy issues raised by SPARS technology and (2) the effort to co-design the rehabilitation program. The analysis will be open-ended, with no propositions guiding qualitative data collection, such that analysis can be as inductive as possible [122]. However, analytic insights will draw on the work of Hedgecoe [88,123] to gain insight into the appropriate balance between individual experiences and health system mandates, promoting a careful and critical analysis of the ethical issues outlined earlier.

#### Adherence-Driven Rehabilitation Program Design and Implementation

Adherence-driven rehabilitation and clinical management strategies will be codeveloped by our health sciences, bioengineering, and social sciences and humanities researchers and our principal Knowledge Translation User organization—leveraging input from the qualitative ethical and policy analysis—and our integrated knowledge translation activities. The design efforts will inform individual and program decision making on critical issues such as to whom and how the adherence analysis is presented and how adherence analysis should inform clinical decisions, physiotherapy treatment, resource allocation, and allied health provider engagement and support. Administration, clinician and patient user-interface, and workflow requirements will be confirmed through a user-centered design process detailed (subsequently) in our integrated knowledge translation strategy. The developed clinical process model and needs assessment will inform SPARS implementation from data collection to the presented analysis.

#### Pilot Test

The rehabilitation program will be pilot tested in 20 patients in the third year of research. The validated SPARS will provide the ability to monitor patient adherence to their prescribed home shoulder physiotherapy, allowing the treating physiotherapists and physicians to incorporate this information into their clinical decision making in accordance with the parameters of the program design. Baseline adherence predictors, inertial data, and clinical outcomes will be captured and stored as specified for the clinical validation study. Qualitative interviews will be conducted with patients, physicians, and stakeholders involved in the pilot program, for examination and analysis of postimplementation perspectives and challenges in accordance with Yin’s case study methodology [122]. Clinical end points and program cost-efficacy will be assessed in comparison with the matched historical controls involved in the validation study.

### Data Analysis

#### Sample Size

The proposed sample size of 120 for clinical validation yields a power of 80% to detect weak correlations (*R*>0.25) between physiotherapy adherence and clinical outcomes, accepting a 5% alpha error. Sample size feasibility was confirmed by the WCP, anticipating a recruitment rate of 70%. The pilot study sample size (20) was used to detect implementation challenges with an incidence rate greater than 15% at a 95% confidence level [124] (not statistically significant differences in clinical or economic outcomes).

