#### Aim 2: Measure the Rate of Adherence to Home Shoulder Physiotherapy, the Relationship Between Adherence and Recovery, and Identify Barriers to Home Physiotherapy Adherence

##### Objectives

The related objectives are as follows:

Inertial sensor data are collected during home physiotherapy for 120 patients with rotator cuff pathology over full treatment duration (up to 5 months).Technical failures preventing home data collection are less than 5%.Clinical outcomes: return to work status, shoulder range of motion, rotator cuff strength, and patient-reported outcomes of pain and disability are collected pretreatment, monthly through treatment (up to 5 months), and at 12-months final follow-up. The final follow-up exceeds 85%.A total of 23 potentially significant predictors of home physiotherapy adherence (identified in Methods: Barriers to Adherence) are collected for all study participants at the time of recruitment.

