##### Hypotheses

The related hypotheses are as follows:

Exercise technique adherence is better for supervised sessions than at home (*P*<.05).There will be a statistically significant association (*P*<.05) between home physiotherapy exercise participation and technique adherence and the identified clinical outcomes.

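### The 80% power for R>0.25 assumes all 120 enrolled patients are analysable; at the plan's own 85% follow-up floor, 12-month power is about 72-73%

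*Protocol article*

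**What the plan says.** Under Data Analysis, Sample Size, the protocol article states: "The proposed sample size of 120 for clinical validation yields a power of 80% to detect weak correlations" above R=0.25 "between physiotherapy adherence and clinical outcomes, accepting a 5% alpha error". It does not say whether the test is one- or two-sided. It names no adherence measure, outcome or time point for the figure. The only other rate given for the cohort is about enrolment: "Sample size feasibility was confirmed by the WCP, anticipating a recruitment rate of 70" per cent.

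The Aim 2 Objectives set the retention target: "The final follow-up exceeds 85" per cent. They set a separate target for the sensors: "Technical failures preventing home data collection are less than 5" per cent. They list five clinical outcomes (work status, range of motion, strength, pain, disability), with collection before treatment, monthly during treatment and at 12 months. The section Clinical and Return to Work Outcomes Data restricts the 12-month visit to its first three items: work status, NPRS and DASH.

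The second Aim 2 hypothesis expects a significant association at P<.05 "between home physiotherapy exercise participation and technique adherence and the identified clinical outcomes". Criterion Validity plans univariate linear regressions for both concurrent and predictive effects.

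**The concern.** The power statement and the follow-up target describe different numbers of patients. The first counts everyone enrolled. The second treats a loss of almost 15% by the final visit as success. If the 12-month outcome is among those the power figure covers, the plan can meet all its own objectives and still lack the power it states.

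The link between adherence and recovery is a main aim of the cohort phase, so this affects how a negative result is read. Someone seeing no significant 12-month association would take it that a correlation of 0.25 had been looked for with 80% power. Because the sentence is tied to no particular association or visit, the reader cannot tell whether the figure is meant to hold at 12 months at all.

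**Working it through.** **Inputs.** N=120, R=0.25, alpha 5% and power 80% come from Sample Size. The final follow-up target above 85% comes from the Aim 2 Objectives. A two-sided test is assumed, because one-sided 5% at N=120 gives 86.8% to 87.9% and so does not match the stated 80%.

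**Step 1: reproduce the stated figure (N=120).**
- Fisher z: power = Φ(atanh(R)·√(N−3) − 1.960). With atanh(0.25)=0.2554 and √117=10.817, this is Φ(2.763 − 1.960) = Φ(0.803) = 78.9%.
- Noncentral t for a regression slope, the analysis that Criterion Validity plans: noncentrality = R/√(1−R²)·√N = 0.2582 × 10.954 = 2.828 on 118 degrees of freedom. Power is 80.1%.
- A simulation of bivariate normal data (200,000 replicates) gives 79.1%.

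The stated 80% is therefore right for one two-sided test with 120 complete pairs. There is no reserve: solving Fisher z for N gives ((1.960+0.842)/0.2554)² + 3 = 123.3, or 124, and the noncentral t reaches 80% at about 120.

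**Step 2: apply the plan's own follow-up floor.** 0.85 × 120 = 102. (The smallest whole number strictly above 85% is 103, which changes nothing material.)

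| Method, R=0.25, two-sided 5% | N=120 | N=102 |
|---|---|---|
| Fisher z | 78.9% | 72.0% |
| Noncentral t | 80.1% | 73.3% |
| Simulation | 79.1% | 72.3% |

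Fisher z at 102: Φ(0.2554 × √99 − 1.960) = Φ(2.541 − 1.960) = Φ(0.581) = 72.0%.

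**Step 3: correlation detectable with 80% power (Fisher z).** R = tanh((1.960+0.842)/√(N−3)). This gives 0.253 at N=120, 0.273 at N=103 and 0.274 at N=102.

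**Step 4: which associations exist at 12 months.** Two adherence measures (participation, technique) with five outcomes give 2 × 5 = 10 pairs over the plan as a whole. If the 12-month visit collects all five outcomes, as the Aim 2 Objectives say, all ten exist there. If it collects only the first three, as the outcomes section says, 2 × 3 = 6 exist. The two sections cannot both hold. The 72-73% is power for each single test at an unadjusted 5%, not power across the set.

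**The case against.** The best defence is that the sentence contains no error. The planned analysis is a regression, and the matching calculation gives 80.1% at 120. This stands: a reader might infer a miscalculation from the Fisher-z requirement of 124, but that is a slightly conservative approximation and the documents do not support the inference.

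Second, Sample Size never mentions 12 months. Outcomes are also collected monthly during treatment, and no loss is stated for those. This also stands, and it confines the shortfall to analyses of the 12-month outcome.

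Third, 85% is a floor, and early retention looks better: 2 of 46 consenting patients had left by December 2019. That is fair, but recruitment had begun only in July 2019, so it says nothing about 12-month loss. A power statement should hold at the retention the plan would accept.

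Three stronger readings are tempting but not supported:
- *About 97 analysable patients and 70% power*, from taking off a further 5% for sensor failure. The documents do not say that the 5% counts whole patients, or patients other than those lost to follow-up. Adherence is summarised in 2-week intervals, so a failed recording need not remove a patient.
- *Ten tests, all at 72%.* If the outcomes section is right, only six pairs exist at 12 months.
- *A 40% chance of a false positive over ten tests.* This is 1 − 0.95¹⁰ and assumes independent tests with no true association anywhere. Outcomes of the same shoulder are likely to be correlated, which lowers it. Rules for multiple testing are also commonly left to an analysis plan, which is not shown.

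Finally, moving from 0.25 to about 0.27 is a small change, and both are weak correlations. That limits the seriousness of the point, but it does not make the stated figure right at 12 months.

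**Conclusion.** The point holds in a limited form. The 80% is correct for one association, tested two-sided at 5%, with all 120 patients analysable. It carries no allowance for loss; the 70% in the same section is a recruitment rate. At the lowest final follow-up the plan accepts, about 102 patients, 12-month power for R=0.25 is about 72-73%, a shortfall of roughly 7 percentage points. The correlation detectable with 80% power is then about 0.27.

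This rests on three assumptions: a two-sided test, follow-up at the floor of its target, and analysis of patients with a 12-month outcome only. A one-sided 5% test would still give 81.5% to 82.8% at 102, but it does not fit the stated 80% at 120. Analyses of on-treatment outcomes may keep the claimed power. The lack of a multiplicity rule in a condensed article is not part of this conclusion. What can be said from the text is that the power figure is attached to no named association or visit. The correction is worth making but does not threaten the design.

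**What to change.** Restate the Sample Size sentence: 120 enrolled; about 102 analysable at 12 months at the follow-up floor; 80% power for R of about 0.27 (about 72-73% for R=0.25), for a single test at an unadjusted two-sided 5%. Add which adherence measure, outcome and time point the figure refers to. If it is meant for an on-treatment outcome, say so and give the loss expected there.

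Reconcile the Aim 2 Objectives (all five outcomes at 12 months) with Clinical and Return to Work Outcomes Data (first three items only), since this decides which associations can be tested at 12 months.

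The cost is a few words in two or three places and a slightly less favourable stated figure. No extra patients are needed. For comparison, keeping 80% at R=0.25 with 15% loss would mean enrolling 120/0.85 = 142 (noncentral t) to 124/0.85 = 146 (Fisher z).
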